#### Descriptive Analysis

A descriptive analysis will be performed on the socio-demographic data, considering vulnerability factors, the family's experience of the intervention, the reasons given for refusing to take part in the research program, and the discontinuations.

#### Comparative Analysis

The effects of the support will be assessed by comparison with the control group. The student's *t*-test will be used for the comparative analyses of the quantitative variables. The chi-squared (χ^2^*)* test will be used for the comparative analyses of the qualitative variables. We will also compare the basic characteristics of populations who refused to take part with those who agreed to be included in the study.

#### Correlation Analysis

Spearman's rank correlation coefficient will be used to test the correlations between the scores obtained on the different scales and the impact of the parental representations on the scores obtained with the different scales.

#### Longitudinal Assessment

A longitudinal assessment will be carried out for both groups to measure the evolution of the test scores from the fourth to the 24th month. A Cox model will be used, with the baby's development (under/over average development) as principal judgment criteria.

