#### Determination of Sample Size

A calculation of sample size was carried out with one case per one control, a power of 80%, an alpha risk of 5%, a global developmental delay (obtained with the BLR test) prevalence rate of 50% in the controls and 25% in the children on the program (based on INTERREG results). The result obtained is a sample of 58 people in the intervention group and 58 in the control group. Taking into account the potential loss of 10% of subjects over the course of this ongoing research, 64 subjects were originally recruited for the intervention group and 64 subjects in the control group.

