##### Evaluation in Both Groups

To check the initial homogeneity of the groups, we proposed an early comparison of the groups with 10 families from each group, randomly selected by a double-blind process. An independent psychologist assessed the baby's development during the first 30 days after birth.

Two HVs are carried out by SB (and the family's dedicated PMI nurse in the “intervention” group), with the parents, taking place when the child is 4 and 24 months old. The purpose is to assess three things: the child's development, parenting, and parent-child interaction. The assessment tools are described in Table 3.

**Table 3 T3:** Outcome criteria and assessment schedule.

**Instrument**	**Concept measured**	**Validation**	**Outcome assessment place of evaluation**	**Structure of instrument; scoring**	**Time of measurement**				**Group**	
					**0**	**4**	**24**	**4**	**I**	**T**

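### The Cox model named for the principal criterion does not fit a reversible status seen at two fixed visits, and is not reconciled with the two-proportion sample size or the chi-squared comparison

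*Protocol article*

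**What the plan says.** Four parts of the protocol article bear on how the principal criterion is analysed.

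- **Longitudinal Assessment** aims "to measure the evolution of the test scores from the fourth to the 24th month" and continues: "A Cox model will be used, with the baby's development (under/over average development) as principal judgment criteria". No event, time origin or censoring rule is given.
- **Evaluation in Both Groups** describes two assessment visits, "taking place when the child is 4 and 24 months old". Table 3 lists the Brunet-Lézine at those two ages only.
- **Determination of Sample Size** assumes "a global developmental delay (obtained with the BLR test) prevalence rate of 50% in the controls and 25% in the children on the program", with "one case per one control", 80% power and 5% alpha. It concludes: "The result obtained is a sample of 58 people in the intervention group and 58 in the control group". Recruitment was 64 per group to allow for 10% loss.
- **Comparative Analysis** says that effects are assessed against the control group. Student's t is given for quantitative variables, and the chi-squared "test will be used for the comparative analyses of the qualitative variables". It does not mention the principal criterion.

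Outline of the Trial and Hypotheses expects less developmental delay in the intervention group at 24 months. Data Collection says that most assessments were placed at 24 months to serve the primary objective. Objectives of the PERL Study makes the comparison of delay prevalence between groups the main objective, and the longitudinal analysis from month 4 to month 24 the secondary one.

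**The concern.** A Cox model compares the rate at which an event happens over observed time. Here the outcome is a status, recorded twice, at ages fixed by design. A child can be below average at 4 months and above at 24, or the reverse, so the status is not absorbing and its onset is never seen. At most two nominal event times exist, and almost every event is tied at one of them.

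The analysis sections name the principal criterion only once, and there they attach this model to it. The hypothesis and the sample size both concern the proportion delayed at 24 months. The trial is therefore sized for one analysis, while its principal criterion is named under another. If the two analyses disagreed, the article gives no rule for which one answers the main question.

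**Working it through.** **1. Reproduce the planned size.** Inputs from Determination of Sample Size: p1 = 0.50, p2 = 0.25, 1:1 allocation, alpha 0.05 (sidedness not stated; two-sided assumed), power 0.80. The mean proportion is 0.375.

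n = [1.960·√(2·0.375·0.625) + 0.842·√(0.50·0.50 + 0.25·0.75)]² / 0.25²
= [1.960·0.6847 + 0.842·0.6614]² / 0.0625 = 57.7, so 58 per arm.

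This matches the stated figure. Power is 80.2% at 58 per arm and 84.0% at 64. No hazard ratio or event count is needed, so the stated size is that of a chi-squared comparison of two prevalences.

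**2. What a Cox model would do with two visits.** The article does not define the event, so two codings are tried. Both keep 58 per arm and 50% v 25% at 24 months. Below-average status and delay are treated as the same binary status. The 4-month prevalence q is not given and is assumed equal in both arms. The test is the Cox score test with exact ties. At each event time, with d events among n children, n1 of them in control and n2 in intervention, the observed-minus-expected control count has variance d·(n1·n2/n²)·(n−d)/(n−1).

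*Coding A: one event time, at 24 months.* Expected events are 29 and 14.5.
- Observed minus expected = 29 − 21.75 = 7.25
- Variance = 43.5·0.25·72.5/115 = 6.86
- z = 7.25/2.62 = 2.77
- Power ≈ Φ(2.77 − 1.96) = 79% by this approximation, and 80% by simulation. The chi-squared test gives the same 80% in the same simulations.

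*Coding B: the event is the first below-average result, at 4 or 24 months.* A child below average at 4 months leaves the risk set, so that child's 24-month result is unused. Worked example with q = 20% and no correlation between visits:
- At 4 months: 11.6 events per arm, contributing 0 to observed minus expected. Variance = 23.2·0.25·92.8/115 = 4.68.
- At 24 months: 46.4 at risk per arm, 23.2 v 11.6 events, contributing 23.2 − 17.4 = 5.8. Variance = 34.8·0.25·58/91.8 = 5.50.
- z = 5.8/√10.18 = 1.82
- Power ≈ Φ(1.82 − 1.96) = 44%.

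The last column below simulates 400,000 trials per setting. It assumes a correlation of 0.2 to 0.5 between the underlying developmental levels at the two visits.

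| q at 4 months (assumed) | 24-month results unused | Power, hand calculation, no correlation | Power, simulated |
|---|---|---|---|
| 0% | none | 79% | 80% |
| 10% | 10% | 59% | 60-62% |
| 20% | 20% | 44% | 44-45% |
| 50% | 50% | 20% | 16-18% |

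The 4-month events carry no arm difference under this assumption. They add variance without signal and remove children from the informative comparison.

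**The case against.** The strongest reply is that the right test is already in the plan. Comparative Analysis promises a comparison with control and a chi-squared test for qualitative variables, and the article schedules the comparative analysis for after the 24-month evaluations. The Cox sentence sits under the longitudinal heading, and the longitudinal question is the secondary objective. On that reading the main comparison is the chi-squared test, with the planned 80.2% power.

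Most of this stands, and it limits the point. A reader might infer that the plan discards the 24-month outcomes, or that the stated 80% power is not delivered. The documents do not support either as a flat statement. Both need first-event coding, which the article does not state. Only children already below average at 4 months would lose their later result, and the loss of power depends on a 4-month prevalence that is not given. With month 4 as origin and a single event time at 24 months, nothing is lost under exact ties. The rule for ties is commonly left to an analysis plan and is not counted here.

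A reader might also infer that using actual visit ages as event times would turn scheduling differences between arms into a false effect. The article says that the family's nurse also attends intervention-group visits, but reports no lag, so no error rate can be attached.

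The reply does not remove the conflict. The chi-squared sentence is generic, the Cox sentence is the only analysis statement that names the principal criterion, and no sentence ranks the two.

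**Conclusion.** The concern holds in limited form. The Cox model is unsuitable for a reversible two-visit status and is inconsistent with the basis of the sample size and with the 24-month hypothesis. The article leaves open which analysis decides the principal criterion.

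The practical effect runs from none to severe. Power stays at about 80% if the chi-squared test decides, or if the Cox model uses a single 24-month time with exact ties. Under first-event coding it falls to about 60-62%, 44-45% or 16-18% at an assumed 4-month prevalence of 10%, 20% or 50%. Those figures rest on equal 4-month prevalence in the arms, the assumed correlation between visits, exact ties and 58 analysed per arm. They show what the ambiguity could cost and do not predict the trial's result.

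**What to change.** In Longitudinal Assessment, delete the Cox model. State that the principal criterion is decided by the between-arm comparison of Brunet-Lézine delay at 24 months, using the chi-squared test already in Comparative Analysis, so that it matches Determination of Sample Size. Report it as a risk difference with a 95% confidence interval.

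For the secondary question of change from 4 to 24 months, use a repeated-measures model with both visits as outcomes (GEE or a mixed model with arm, visit and arm-by-visit terms), and read the arm difference at each visit.

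The cost is one paragraph of analysis wording, to be settled before the 24-month comparison is run. No new data, staff or participants are needed.

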## Discussion

### Expected Findings

The PERL study proposes and evaluates preventive intervention home support starting at the earliest age to support parent-child interactions and the child's development, which is integrated into the HVs made by PMI nurses. In line with the priorities set out in the national health policy, this action-research project is in keeping with the principle of reducing social inequalities in healthcare access in France.

### Strengths and Limitations

In the PERL study, the intervention is available to the general population, without applying vulnerability criteria as is usually the case (94–97). PMI is a universal service, accessible to the general population. Recruitment is carried out via a universal approach, by making the same system available to the population, irrespective of social status. According to work conducted by the University of British Columbia (34), child vulnerability exists in all socioeconomic layers of our society and the majority of vulnerable children are found in families with middle-class socioeconomic status. The PERL study approach is available to all families who attend the meeting at the recruitment stage where HVs are proposed. No meetings are arranged with families who refuse from the outset.

The first limitation of this system is that families have several opportunities to refuse before they are included in the study. A system of natural selection is therefore in place and families who agree to participate have demonstrated their motivation and desire to receive preventive support regularly. The involvement of families is key in the success of the PERL study (16, 94). It was not possible to meet families during their visits to maternity hospitals given the high number of maternity hospitals involved (5) and their geographical spread (1,576 km^2^), which would have allowed us to limit the opportunity to refuse participation.

The second limitation concerns the constant and necessary adaptation to the difficulties encountered in the field, as reported by the PMI nurses. The PERL study protocol was based on recognized theoretical bases that are transferable into current PMI practices. However, as for all action research, adaptations were necessary due to professional constraints (time allocated to the tool, lack of staff, and adaptation of training, etc.) and comments from PMI nurses regarding the practical implementation of the protocol in the field.

The third limitation concerns a possible contagion effect between the two groups of the study. Most of the PMI nurses in the trial area were taking part in the PERL study and so receive the training and supervision and are involved in working and exchange days. They are therefore all confronted with a potential change to their routine practice. We will therefore identify the families of the control group benefiting from a “traditional” PMI follow-up.

This information is collected during the assessment HVs (at 4 and 24 months). In the case of 525 the PERL study, PMI nurses needed to change their practices. These changes took place on several levels. First, from a structural and organizational point of view, it influences and encourages dedicated time for training, supervision, and analysis of practices. Second, the HVs and the PMI nurses: use more observation for some or more play; are less direct in the exchanges; actively aim to highlight parenting skills; adapt the advice they provide to parental requests through guidance; and do not give identical advice to all parents (prevention recommendations). A third change took place in that, undertaking more HVs than usual allows PMI nurses to respect the parenting process, which is set up at different stages for each parent. Previously, the PMI nurses conducted a single postnatal HV for families that were not classed as vulnerable, mainly primiparous, and when the workload allowed. They would then give all the prevention recommendations during this single HV and make themselves available for follow-ups if needed. The meetings could be very directive and place little focus on the dimension of early mother-child interactions or the mother's thymia. For so-called vulnerable families, the follow-ups could be more “educational”, with objectives that the PMI nurse would set, but not necessarily at the parents' request.

There are further limitations concerning the fact that SB is involved in promoting the study, recruitment, and conducting/processing assessments. To address this, tests will be analyzed blindly by the coordinator and other psychologists working on the protocol for video-based tests (Mini Q-SORT, AQS, early interactions at Bobigny, Brunet Lézine revised). The ADBB test will be analyzed by other trained professionals.

Early referrals may also be made to specialist therapy services (in particular for the intervention group), which may impact the scores in some tests. The purpose of early prevention programs is to direct parents, from the outset, to care services and organizations that can support them with their difficulties (care services, social services, etc.) (27–30, 34).

The final limitation lies in the small sample size of the study. We are well-aware that, given the small sample size, we may not be able to highlight any significant difference on the primary endpoint but will, however, gain quantitative and qualitative indicators of the impact of this device. In addition, if the results on the scales are not significant, a qualitative analysis of the results will be carried out.

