#### Sample Characteristics

- Eligibility criteria

There were two eligibility criteria: (i) the child was to have been born between September 2018 and December 2019 in the general population; and (ii) all families had their main residence in the *Pays Lunévillois*, in Lorraine, France.

- Exclusion criteria

There were three exclusion criteria: (i) a child born prematurely, before 37 weeks of pregnancy; (ii) families that did not speak French; (iii) non-settled traveler families, temporary refugees, and families with no fixed abode.

Participants were not prohibited from taking part in other research projects during this trial.

- Randomization (Figure 1)1) Every month, the PMI service sent the coordinating psychologist (SB) a list of all pregnancies reported in the population residing in the recruitment area, in the seventh month of pregnancy (on average 60 births per month).2) SB then sent a letter to all of the families on the list, informing them that research was being conducted and that they were likely to be contacted and invited to participate. This letter informed the families that they had 2 weeks to refuse participation.3) Two weeks later, SB performed the randomization process (Zelen randomization with a double consent for the 2 groups) based on the updated list of reported pregnancies post-refusal and returns for wrong address after the first letter had been sent. The families were thus randomly assigned to either the “intervention” or the “control” group.4) SB then sent a second letter informing families that they have been randomly selected to take part in the PERL study and forwarded a brochure describing the terms of participation (purpose of the study, how to participate, a presentation of the relevant stakeholders) with a suggested date for an HV (the start of the 8th month of pregnancy).5) If no refusal was received from the families, SB performed the HV to outline the trial to them, and if they agree to take part in the study they were asked to sign consent forms.

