**Figure 1 F1:**
[figure not shown]
Recruiting method of the PERL study.

This recruitment method was highly formalized to meet the needs of research. Families were randomized in accordance with Zelen randomization before consent was requested to prevent the families' preference for one or another group and to avoid disappointment at not being in the intervention bracket. However, all parents may benefit from the PERL study: control group parents still had two assessments of their child's development, which could be reassuring. As double-blind evaluation cannot be performed in the PERL study, to circumvent this limitation, analysis will be performed by a professional who does not know the attribution group.

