					**Mths after birth years**					
Neonatal Brazelton Assessment Scale (NBAS)	Neonatal behavior (0–1 month)	Brazelton e (58) (3° ed)	Psychologist at the maternity hospital/home visit	The assessment concerns: autonomic system motor tone organization state organization and regulation early interaction	X				X	X
Brunet-Lézine Revised Developmental test	Child development (2–30 months)	Brunet and Lézine, 1965 (59)	Psychologist during home visits	Developmental age (developmental quotient)4 dimensions: Language Social relationships Motor gross Motor fine 30 item test scored partly		X	X		X	X
Alarm Baby Distress scale (ADBB)	Sustained withdrawal behavior (2–24 months)	Original scale in FrenchGuedeney and Fermanian (60) in France	Psychologist, after home visits, with video	8 items, 5 point Likert scale (0–4), range 0–32 Withdrawal behavior if ≥ 5		X	X		X	X
Symptom Check-list (SCL-90)	Mother's psychological disorders	Derogatis (61) Translation	Mother during home visits	90 items, 5 point-Likert scales (0–4) X X X10 subscales: Somatization (0–48) Obsessive-Compulsive (0–40) Interpersonal Sensitivity (0–36) Depression (0–52) Anxiety (0–40) Hostility (0–24) Phobic Anxiety (0–32) Paranoid Ideation (0–24) Psychoticism (0–40) Other symptoms (0–28) Higher scores indicate greater Clinical impairment.		X	X		X	X
Working Alliance Inventory (WAI)	Working alliance between the mother and the pediatric nurse	Horvath and Greenberg (62) French validation Guedeney et al. (63)	Mother and pediatric nurse after home visits	12 items, Likert scale (1–7) Range 12–84 Higher scores indicates better working alliance		X	X		X	
Attachment Q-Sort (AQS)	Child's attachment (10 months−3 years)	Waters and Deane (64) French translation made and validated by a panel of infant mental health experts (65)	Assessment team (psychologist and nurse) after home visits	Two rates assess each situation during a home visit of 2 h90 itemsCorrelation with typical secure pattern: Insecure attachment if <0.35 Secure attachment if ≥ 0.35			X		X	X
Edinburgh Postnatal Depression Scale (EPDS)	Self-Assessment of postpartum depression	Cox et al. (66) French validation: Guedeney and Fermanian (67)	Mother during home visits	10 items, 4 point-Likert scales (0–3) Range 0–30 Higher scores indicate higher levels of depressive symptoms.		X			X	X

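### The coordinating psychologist is named as a blind scorer of Brunet-Lézine and three other observer-rated tests, but knows every family's arm; the article also disagrees with itself on how Brunet-Lézine and AQS are rated

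*Protocol article*

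**What the plan says.** Under Sample Characteristics, the text below Figure 1 accepts that a double-blind evaluation is impossible and says that "analysis will be performed by a professional who does not know the attribution group". Strengths and Limitations returns to the subject. It concedes that one person promotes the study, recruits, and conducts and processes the assessments, and then states: "To address this, tests will be analyzed blindly by the coordinator and other psychologists working on the protocol for video-based tests". The tests covered are "Mini Q-SORT, AQS, early interactions at Bobigny, Brunet Lézine revised". ADBB is given to other trained professionals.

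Elsewhere the article describes the coordinator's roles:
- Sample Characteristics: the coordinator "performed the randomization process (Zelen randomization with a double consent for the 2 groups", and afterwards made the home visit at which consent was sought.
- Evaluation in Both Groups: the coordinator carries out the 4- and 24-month visits, joined by others in one arm only ("and the family's dedicated PMI nurse in the" intervention group).
- Supervision: the coordinator and a child psychologist supervise the intervention nurses monthly.

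Table 3 has Brunet-Lézine done by a psychologist at the home visit. For AQS it gives the raters as "Assessment team (psychologist and nurse) after home visits" and marks the test for both groups.

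**The concern.** The remedy relies on the person whose several roles created the problem. Someone who drew the allocation, and who sees the family's nurse at the intervention visits, cannot score those families without knowing the arm.

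This matters most for Brunet-Lézine. Determination of Sample Size is built on global developmental delay by that test, 50% in controls against 25% with the programme, and the scoring calls for an examiner's judgement. Mini Q-Sort, the Bobigny grid and AQS are also observer-rated. A modest tendency to score intervention children more favourably would look like a programme effect, and no later analysis could separate the two. A reader would also take the results as blind-scored when some were not.

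Test conditions are a second issue. In the intervention arm the child may be tested with a familiar nurse in the room; in the control arm no nurse is described. If a nurse is also an AQS rater, the rating team may differ by arm.

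**Working it through.** **Step 1: can the coordinator be blind?** Three sections bear on this. In Sample Characteristics the coordinator allocates families and meets them after allocation. In Evaluation in Both Groups the coordinator conducts both evaluations, with the family's nurse present in one arm only. In Supervision the coordinator discusses the intervention families' follow-up with their nurses. Each of these alone reveals the arm. The blinding stated in Strengths and Limitations therefore cannot hold for this scorer.

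**Step 2: how are the tests rated?**
- Brunet-Lézine: Table 3 places it with the psychologist at the visit; Strengths and Limitations lists it as video-based. The article does not say which score is analysed.
- AQS: Table 3 names a psychologist and a nurse after the visit; Strengths and Limitations gives it to psychologists as a video-based test. The only nurse described at an evaluation visit is the intervention family's own, and the second rater for control families is not identified.
- ADBB: other trained professionals.
- SCL-90, EPDS, BDI and BITSEA: completed by the mother.

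**Step 3: the plan's own figure.** Inputs from Determination of Sample Size: p1 = 0.50, p2 = 0.25, 1:1 allocation, power 80%, alpha 5% (taken as two-sided). With pooled p = 0.375:

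n = [1.96·√(2·0.375·0.625) + 0.8416·√(0.50·0.50 + 0.25·0.75)]² / 0.25² = (1.342 + 0.557)² / 0.0625 = 57.7, so 58 per group.

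This reproduces the stated 58. Allowing for loss, 58 × 1.1 = 63.8, which gives the stated 64. There is no sample-size error in this point.

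**Step 4: what scoring bias could do.** The documents give no bias size, so a range is assumed. Take no true effect, a 50% delay rate, n = 58 per arm, and a recorded rate of 0.50 − b in the intervention arm. With p̄ the mean of the two recorded rates:

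P(significant in favour) = Φ[(b − 1.96·SE0)/SE1], where SE0 = √(2·p̄(1 − p̄)/58) and SE1 = √{[0.25 + (0.50 − b)(0.50 + b)]/58}.

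| b | share of planned 25 points | SE0 | SE1 | z | probability |
|---|---|---|---|---|---|
| 0 | 0 | – | – | – | 2.5% |
| 0.05 | 20% | 0.0927 | 0.0926 | −1.42 | about 8% |
| 0.08 | 32% | 0.0926 | 0.0923 | −1.10 | 13–14% |
| 0.10 | 40% | 0.0924 | 0.0919 | −0.88 | about 19% |
| 0.15 | 60% | 0.0918 | 0.0907 | −0.33 | about 37% |

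The 8-point row corresponds to a shift of 0.2 SD on a normally distributed score cut at its mean, since Φ(−0.2) = 0.42.

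**The case against.** The article discloses the limits of blinding and the coordinator's mixed roles, and it names other psychologists as well as the coordinator. If those others scored alone from video they might be masked. A reader might therefore infer that the trial has no blind assessment at all, and the documents do not support that: masked scoring by the others is possible and ADBB is assigned elsewhere. What remains is that the text does not give the four tests to the others alone, and a nurse visible on film could still reveal the arm.

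Three other stronger readings are tempting and should not be adopted.
- That the intervention family's nurse rates her own family on AQS. This follows only from joining Table 3 to Evaluation in Both Groups. Table 3 does not say which nurse, and Strengths and Limitations assigns AQS to psychologists.
- That most secondary outcomes are affected. Four of the scales are completed by the mother, so the coordinator's scoring does not reach them, although the nurse may be present while they are filled in.
- That Brunet-Lézine is not scored from video. Table 3 points to a live assessment, the Discussion to video, and the consent section to filming for scoring. The conflict is real but the documents do not settle it.

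The sentence below Figure 1 may also refer to data analysis and not to scoring. It sits badly with the coordinator as scorer, but the contradiction does not depend on it.

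**Conclusion.** The point stands in a limited form. Blind scoring by the coordinator is impossible on the article's own account, and it is claimed for the test behind the sample size and for three other observer-rated instruments. The sections on who rates Brunet-Lézine and AQS, and how, do not agree, and the nurse's attendance makes test conditions differ by arm.

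The chance of a false significant benefit runs from about 8% to 37% over assumed biases of 5 to 15 points, against 2.5% without bias. This is an illustration that rests on no true effect, a 50% delay rate and 58 analysed per arm; it does not estimate the bias in this trial. The conclusion about the coordinator needs none of these assumptions. It should be corrected before the 24-month comparison, which the article places from 2022.

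**What to change.** - Remove the coordinator from scoring for the analysis. Take the primary Brunet-Lézine score, and the Mini Q-Sort and Bobigny scores, from video, rated by psychologists already on the protocol who have no part in allocation, visits, nurse supervision or delivery. This also excludes the child psychologist who co-supervises the nurses. Clips should show no nurse.
- Keep the coordinator's live Brunet-Lézine score as an agreement check, and flag items that can only be scored live.
- For AQS, use the same type of raters in both arms and never the family's own nurse. Table 3 describes a 2-hour visit, and nothing shows that all of it is filmed; where it was not, report AQS as unblinded.
- Keep the nurse out of the testing part of the remaining visits, or record her presence.
- State that test administration is unblinded, and reconcile the text below Figure 1, Evaluation in Both Groups, Table 3, and Strengths and Limitations.

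The cost is reassigning scoring among existing staff and some video work, using recordings for which parents already sign consent. No new instrument or visit is needed. The drawback is that some items will remain scored live by someone who knows the arm.
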